### Outcomes

The *primary outcome* is HIV prevalence in young women aged 15–29 years, measured in an impact survey in the five intervention and five control (second wave of intervention) districts. We will undertake rapid HIV screening testing, using Alere Determine units to test finger prick blood samples for HIV1 and HIV2 antibodies. We will not perform confirmatory testing for those that test reactive on this screening test. However, those reactive on the screening test will be referred to their local government clinic for confirmatory testing, counselling, and treatment if appropriate.

*Secondary outcomes* will rely on responses to a questionnaire for men and women aged 15–29 years administered in the impact survey in intervention and control districts. We will measure intermediate outcomes between knowledge and behaviour, according to the CASCADA behaviour change model [55, 56], based on the Theory of Planned Behaviour [57]. CASCADA is an acronym for a partial order of intermediates between knowledge and action: Conscious knowledge, Attitudes, Subjective norms, intention to Change, Agency to make the change, Discussion with family, peers and neighbours, and finally Action. The model does not assume that intermediate steps between conscious knowledge and action are necessarily linearly related. We have used the CASCADA model in resource-poor settings to support analysis and interpretation in cross-sectional studies examining health-related behaviours [58, 59], to guide design of interventions [50, 60, 61] and as a framework for qualitative and quantitative analysis of intervention effects [62, 63]. In this trial, the questionnaire will collect information on the CASCADA sequence of intermediate variables for use of government programs, engagement in transactional sex, gender violence, physical intimate partner violence, multiple partners, and condom use.

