### Sample size

The intervention package will potentially affect all young women in each intervention district. However, the impact assessment will rely on a cluster random sample of communities drawn from the recent census. There are thus two quite different domains – the domain of intervention (*all* young women in the intervention districts) and the domain of the survey (the *sample* of villages or clusters that will provide evidence of the impact on young women in the district) within which we will include all young women with no sub-sampling within the cluster.

Sample size calculations for the survey used a calculator developed by Taylor and colleagues [64]. The HIV prevalence in Botswana control clusters in the 2012 impact assessment was 23% among women aged 15–29 years ([name], personal communication). In the Botswana AIDS Impact Survey of 2013, the HIV prevalence among women aged 15–49 years was 28.2% [39]. Since districts are the unit of randomization, intervention and analysis, starting from 23% (range 17–28%, k = 0.119), 650 women per district in five districts in each arm would detect a reduction to 17.25% (25% reduction in HIV) at the 5% significance level with 80% power. In the unpublished three-country study, the combined interventions in Botswana produced a reduction in HIV of around 50% ([name], personal communication); these sample size calculations therefore allow for some inefficiency in taking the interventions to scale.

We will select a stratified random sample of 10 clusters (enumeration areas) from each of the five intervention districts, and 10 from the control (next wave of intervention) districts. From each cluster we will interview and test for HIV (rapid screening testing of finger prick blood) around 100 young people aged 15–29 years (at least 65 of them women). The sample will include around 5000 people from intervention districts and 5000 from non-intervention districts. To achieve these numbers, the overall sample size *invited to participate* in the survey will need to be around 7500 to allow for absentees and those who decline to participate. Some 13.1% of young women contacted in the 2012 survey in the three countries declined to participate, and a further 14% were absent at the times the interviewer could visit ([name], personal communication).

Secondary outcomes (such as gender violence, unsafe sexual behaviours) are more common occurrences and the power to detect these is correspondingly greater.

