We will use multiple-imputation to deal with missing data [72]. All statistical tests will be two-sided at the 0.05 level of significance. The Bonferroni method will adjust the level of significance for testing for secondary outcomes to keep the overall level at alpha = 0.05. We will express results as effect or odds ratio/relative risk reduction for binary outcomes, standard errors, corresponding two-sided 95% confidence intervals and associated *p*-values.

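### The statement that secondary outcomes have greater power ignores the plan's own Bonferroni rule and is reversed under the primary outcome's assumptions

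*Protocol article*

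**What the plan says.** All references are to the protocol article.

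- **Sample size, primary outcome.** The calculation is "starting from 23% (range 17–28%, k = 0.119), 650 women per district in five districts in each arm", which "would detect a reduction to 17.25% (25% reduction in HIV) at the 5% significance level with 80% power".
- **Sample size, secondary outcomes.** The section closes by saying that these outcomes, with gender violence and unsafe sexual behaviours as examples, "are more common occurrences and the power to detect these is correspondingly greater". It gives no baseline rate, between-district variation, effect size or number of tests for them.
- **Statistical methods, multiplicity.** "The Bonferroni method will adjust the level of significance for testing for secondary outcomes to keep the overall level at alpha = 0.05". The number of tests in that family is not given.
- **Outcomes.** The questionnaire covers the CASCADA steps for six behaviours: "use of government programs, engagement in transactional sex, gender violence, physical intimate partner violence, multiple partners, and condom use". The seven steps are "Conscious knowledge, Attitudes, Subjective norms, intention to Change, Agency to make the change, Discussion with family, peers and neighbours, and finally Action". Women and men are both surveyed.
- **Statistical methods, test.** The primary analysis is a two-sample t-test with the district as unit, five against five. Secondary comparisons adjust for clustering, and no test is named.

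**The concern.** The power statement reasons from frequency alone: a commoner outcome, so more power. Two features of this design work against that.

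First, there are only ten districts. A commoner outcome reduces the relative sampling error within districts, but it need not reduce the variation between them, and that is already the larger part of the variance for HIV prevalence.

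Second, the secondary outcomes are tested at a stricter level than the primary, and with 8 degrees of freedom a stricter level is expensive.

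Impact on the intermediate outcomes is one of the specific objectives, and these outcomes would be used to explain either a positive or a null HIV result. A reader told that they are better powered than HIV will take non-significant intermediates as evidence that the mechanism failed. Under the primary's assumptions with six tests, a true 25% effect on any one outcome would be missed about half the time.

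**Working it through.** **Inputs from the document.** p0 = 0.23, p1 = 0.1725, k = 0.119, n = 650 women per district, c = 5 districts per arm; two-sided 5% ("All statistical tests will be two-sided at the 0.05 level of significance").

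**Assumed for secondary outcomes, since the document gives no values.** The same k, n and 25% relative reduction; baselines of 30–60%; a district-level t-test on 8 df; m tests, each at 0.05/m.

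**Step 1: reproduce the stated figure.** Let V = [p0(1−p0) + p1(1−p1)]/n + k²(p0² + p1²).

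- Within districts: (0.1771 + 0.1427)/650 = 0.000492.
- Between districts: 0.01416 × (0.0529 + 0.0298) = 0.001170, which is 70% of V = 0.001663.
- Districts per arm: c = 1 + (1.96 + 0.84)² × V/(0.0575)² = 4.95, against the stated 5.
- Power at c = 5: 80.5% by this normal formula (using c − 1), and 78.8% by the noncentral t on 8 df.

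The stated 80% is reproduced.

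**Step 2: make the outcome commoner.** Noncentrality = (p0 − p1)/√(V/5). For p0 = 0.40 and p1 = 0.30: V = 0.45/650 + 0.01416 × 0.25 = 0.000692 + 0.003540 = 0.004233; standard error 0.0291; noncentrality 0.10/0.0291 = 3.44.

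**Step 3: apply 0.05/m.** The critical t values are 2.31 (m = 1), 2.75 (m = 2), 3.48 (m = 6) and 4.90 (m = 42).

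| Baseline → 25% lower | Between-district share of V | Noncentrality | m = 1 | m = 2 | m = 6 | m = 42 |
|---|---|---|---|---|---|---|
| 23% → 17.25% (primary) | 70% | 3.15 | 79% | – | – | – |
| 30% → 22.5% | 77% | 3.30 | 82% | 70% | 48% | 18% |
| 40% → 30% | 84% | 3.44 | 85% | 74% | 53% | 20% |
| 50% → 37.5% | 88% | 3.53 | 87% | 76% | 55% | 22% |
| 60% → 45% | 91% | 3.59 | 88% | 78% | 57% | 23% |

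Here m = 6 is one test per listed behaviour. m = 42 is 7 steps × 6 behaviours, which is a count made for this check and not a figure in the document. With unlimited women per district, power would still be only 91% at m = 1, 62% at m = 6 and 27% at m = 42.

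**Step 4: vary what the document leaves open** (baselines 30–60%, t on 8 df unless stated).

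- Normal formula with c − 1 in place of the t: 76–83% at m = 2, 62–72% at m = 6, 39–49% at m = 42. Its primary power is 80.5%, so under this formula two tests straddle the primary and six fall clearly below it.
- k = 0.15: 67–72% at m = 1, 32–36% at m = 6, 10–12% at m = 42.
- Constant intracluster correlation, 0.119² × 0.23/0.77 = 0.0042, with between-district variance 0.0042 × [p0(1−p0) + p1(1−p1)]: for baselines 30/40/50/60%, 56/78/93/99% at m = 6 and 23/42/64/84% at m = 42.
- 40% relative reduction, k = 0.119: 95–98% at m = 6 and 71–81% at m = 42.
- Same absolute difference as the primary (5.75 points), k = 0.119, m = 1: 58%, 38% and 27% at baselines of 30%, 40% and 50%.

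**The case against.** The strongest defence has four parts.

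1. **At a single 5% test the sentence is right in direction.** With the primary's k and relative reduction, 82–88% exceeds 79%. This stands. But the plan does not test secondary outcomes at a single 5% level, and with k = 0.15 or the same absolute difference the direction fails even there.

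2. **The size of the Bonferroni family is not stated and may be fixed in an analysis plan that is not shown.** This stands. The Outcomes section describes what the questionnaire collects, not 42 confirmatory tests. A reader might infer 42 tests, or 84 with women and men tested separately, and conclude that these analyses have power of only 11–23% and almost none can succeed. The document does not support that. The point needs no such count: with the t-test the reversal appears at two tests, and the article names six behaviours.

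3. **k = 0.119 and the 25% reduction were given for HIV prevalence only, and the 8-df t-test for the primary analysis only.** This also stands. The secondary outcomes lie closer to the intervention, so larger effects are plausible, and a constant intracluster correlation would make commonness worth a good deal. Equally, nothing excludes a larger k. These are reasons why power is unknown, and the article states it as known.

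4. **Primary outcome, randomisation and sample size are untouched.** Agreed.

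**Conclusion.** The sentence does not follow from the plan's own figures. Carrying the primary's k, sample size, district count and 25% relative reduction over to the secondary outcomes, commonness adds between 3 and 9 percentage points, and Bonferroni takes away more than that: 70–78% at two tests, 48–57% at six and about 18–23% at 42, against 79% for the primary.

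These figures are conditional. They rest on k, effect size, number of tests and test method, none of which the article states for secondary outcomes, and Step 4 shows that power at six tests can lie anywhere from about 32% to 99%. The supported conclusion is that the claim is unsupported, and reversed under the primary's assumptions once the multiplicity rule is applied. A reader might go further and call the claim simply false, or read it as a promise of more than 80% power. The article gives no numerical power for secondary outcomes, and some unstated but possible assumptions would make the claim true.

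**What to change.** **Power statement.** Delete the sentence. Alternatively, replace it with power at 0.05/m for the main secondary outcomes, stating the number of tests in the family and, for each outcome, the assumed baseline, k and effect size. This changes text only, with no extra recruitment or fieldwork.

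**Multiplicity method.** Replace Bonferroni with Holm for the secondary family. It keeps the same 5% familywise level and is never less powerful. The gain is limited, because Holm's first step uses the Bonferroni threshold. The small cost is that Holm has no simple matching simultaneous confidence intervals.

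**Optional.** The confirmatory family could be confined to the six Action outcomes in women, with the other steps and the results in men reported descriptively. The error does not require this. It would demote part of the specific objective on intermediate outcomes, which covers young women and young men, and six tests would still have only 48–57% power under the primary's assumptions. The investigators should weigh that trade-off.

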### Allocation

Central randomization of districts will stratify by two factors (1) HIV prevalence (above or below the national average), using results of the fourth Botswana AIDS Impact Survey (BAIS IV) [39] and (2) development and economic status including proportions of urban and rural communities.

An epidemiologist not involved in the fieldwork will centrally randomize districts using an online random number generator, with allocation concealment until commencement of each wave. We will unmask the first wave districts immediately, and the second wave in year 5. Local intervention activities will be obvious to residents in the intervention sites. Knowledge of *future* intervention status may become clear to residents of the second wave at the time of their baseline study, in year 5. Some secondary outcomes (particularly conscious knowledge) could be influenced by knowledge of intervention status. Other indicators like a reduction in gender violence or HIV status would be less susceptible to this bias.

Interviewers in the impact survey will not include intervention fieldworkers and, as far as possible, they will be kept unaware if the communities in which they are interviewing are in intervention or non-intervention districts. The principal analysis will be undertaken blind of intervention status, using only group labels for each district.

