**Methods:**

This parallel group cluster randomised controlled trial compares HIV rates among young women in districts with and without the structural interventions. The 30 administrative districts in the country, stratified by HIV prevalence and development status, will be randomly assigned to 5-district implementation waves. The intervention in the first-wave districts will include: (i) recruiting and preparing vulnerable young women to apply to government support programs, (ii) making the support programs more accessible to young women by engaging local program officers and young women in co-evaluation of programs and co-design of solutions; and (iii) generating an enabling environment for change in communities through an audio-drama edutainment program. In year five, an impact survey will measure HIV rates among vulnerable young women (15–29 years) in a random sample of communities in the five intervention districts and in the five second-wave (control) districts. Fieldworkers will undertake rapid HIV screening and interview young women and young men, collecting information on secondary outcomes of attitudes and behaviours.

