#### Statistical methods

We will adopt an intention-to-treat principle for measuring primary outcomes with district as the unit of analysis. The primary analysis will treat the two groups of districts as a parallel design, and will use a two-sample t-test to compare the HIV prevalence rate of young women aged 15–29 years in the five first wave (intervention) and the five second wave (control) districts. Since the impact assessment in the first wave will coincide with the baseline in the second wave, the analysis will be able to ignore temporal effects.

Secondary analysis will compare HIV and gender violence related knowledge, attitudes and behaviours in young women and men between intervention and non-intervention districts, adjusting for clustering. Adjusted analysis using regression techniques will investigate the residual impact of key baseline characteristics on the outcomes. We will examine the residuals for model assumptions and chi-squared test of goodness-of-fit. Analysis will rely on CIETmap software [70] which provides a windows interface with the statistical programming language R.

We will summarize district demographics and outcome variables (both primary and secondary) using descriptive measures: mean (standard deviation) or range (minimum-maximum) for continuous variables and number (percent) for categorical variables.

Sensitivity analysis will examine correlated outcomes using generalized estimating equations, assuming intervention as a fixed effect, district as clustering variable and an exchangeable or unstructured covariance structure to model correlation of participants within a district. Planned subgroup analysis will focus on subgroups of young women with different exposures [71]. Age is a core issue in gender violence and HIV incidence. A history of sexual abuse is likely to affect responses across a range of themes. Variables on use of alcohol and other substances may be informative, as well as employment or educational status and exposure to workshops in the intervention districts.

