## Discussion

The presently funded project is the first stage of a longer national process implementing an HIV structural prevention package in waves of five districts in a stepped-wedge design. If funding is available, we will start the intervention package in the second wave of districts once the impact survey in the first and second wave districts is completed (in year 5). The second wave intervention package will include modifications based on the experience during the first wave of implementation. With the Government of Botswana, we will seek funding for extension of the intervention and impact measurement from national and international sources. If the first and/or second waves of interventions are successful in reducing HIV infections, the government may decide to roll out the package in all remaining districts as rapidly as possible.

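### Control (second-wave) districts are unmasked in the same year they are surveyed, which leaves open an avoidable part of a bias the protocol itself names for some secondary outcomes

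*Protocol article*

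**What the plan says.** The Allocation section of the protocol article has districts randomised centrally by an epidemiologist outside the fieldwork, "with allocation concealment until commencement of each wave". It then gives the timing: "We will unmask the first wave districts immediately, and the second wave in year 5". The second-wave districts are the control arm of this trial.

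The section goes on to say that knowledge of future "intervention status may become clear to residents of the second wave at the time of their baseline study, in year 5". It names the consequence: "Some secondary outcomes (particularly conscious knowledge) could be influenced by knowledge of intervention status". It adds a limit: "Other indicators like a reduction in gender violence or HIV status would be less susceptible to this bias".

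Three other safeguards or timings bear on the point:

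- Allocation keeps intervention fieldworkers out of the interviewing team, aims as far as possible to keep interviewers ignorant of district status, and has the principal analysis done blind.
- The abstract puts the impact survey in year five, in both arms. Statistical methods confirms the overlap: "Since the impact assessment in the first wave will coincide with the baseline in the second wave", the analysis can set time effects aside.
- The Discussion says that, if funds allow, "we will start the intervention package in the second wave of districts once the impact survey in the first and second wave districts is completed".

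**The concern.** A control district learns nothing from the intervention itself during the trial, so the main way its residents can become aware of allocation is by being told, or by finding out, that they are next. The protocol allows that to happen around the time they answer the questionnaire. All secondary outcomes rest on that questionnaire (Outcomes section). Conscious knowledge, the outcome the protocol picks out as most open to influence, is the first element of the CASCADA sequence used to interpret the others.

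If control residents hear that a programme on access to government support, gender violence and HIV is coming, their answers could shift for that reason alone, and in one arm only. Residents or local leaders who know their wave could also pass it on during house-to-house interviewing, which would weaken the plan to keep interviewers unaware.

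What is at stake is the comparison of the more reactive secondary outcomes. The primary outcome is a finger-prick HIV screening test analysed at district level under blinding, and it is not in play.

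**Working it through.** No figure in the plan depends on this rule, so the check is a comparison of the statements on timing and masking.

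**1. When are control data collected?** In year 5 (abstract). The survey is at once the first-wave impact assessment and the second-wave baseline (Statistical methods). The baseline study mentioned under Allocation is therefore the survey that supplies the control arm's outcome data.

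**2. When is the control arm unmasked?** In year 5 (Allocation). The order within that year is not given, and neither is the audience. The next statement on the second wave, however, places residents' possible awareness at the baseline study. The authors thus foresee that knowledge and measurement may coincide.

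**3. When does the second-wave intervention begin?** After the survey is completed in both waves, subject to funding (Discussion).

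**4. Are the statements compatible?** That depends on what commencement of a wave means, which the article does not define.

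| Reading of commencement | Concealment ends | Fit with the rest |
|---|---|---|
| Start of the intervention | After the survey (Discussion) | Sits badly with Allocation's expectation that residents may know at the survey |
| Baseline survey included | As control data are collected | Consistent, but gives no protection during measurement |

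**5. Does anything stated require earlier disclosure?** Those organising the survey must know which five of the 30 districts are second wave, or they cannot sample them. For residents and interviewers no such need is stated. For local leaders, the Informed consent section seeks agreement in districts randomised to receive the intervention. For the second wave, nothing says that this must happen before the survey.

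**6. Who is exposed?** From Sample size: 5 control districts × 10 clusters × about 100 young people = about 5,000 respondents. With at least 65 women per cluster, 5 × 10 × 65 = at least 3,250 of them are women. These are the people who might be affected. The document gives no way to say how many would learn their status, how far their answers would move, or in which direction.

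**The case against.** The strongest reply is that the protocol has already dealt with this. It promises concealment until each wave commences. Read with the Discussion, that could already mean disclosure after the survey. The remark about residents is a candid limitation and not an instruction to tell them. The timeline figure is not available here, and an article condenses a fuller document. This is fair as far as it goes, and it is why the point cannot be put as a statement that control districts will be told during fieldwork. But the article itself expects awareness at the survey and does not use the gap that the Discussion provides to prevent it.

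Three stronger readings are tempting, and the text does not support them:

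- **That control districts will be publicly identified.** No announcement is planned anywhere.
- **That interviewers will be told the allocation.** The protocol plans the opposite. What can be said is that it does not explain how that plan fits with unmasking in the same year.
- **That every questionnaire outcome is compromised.** The protocol names some secondary outcomes, chiefly conscious knowledge, and regards gender violence as less susceptible. Nothing in the document shows how hearing of a possible future programme would alter reports of past violence or past programme use.

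It can also be said that later disclosure would achieve little. First-wave activities are obvious to residents, so that arm cannot be masked, and the absence of activities may reveal a non-intervention district. A planned subgroup analysis uses workshop exposure. If that exposure is asked about at interview, the answers could show interviewers which arm they are in. This stands: only knowledge of a future, funding-dependent intervention can be withheld, and the gain is partial. Finally, withholding status from second-wave leaders delays discussions with them, which is a real if small cost.

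**Conclusion.** The point holds as a minor one. Unmasking of the control arm and measurement of the control arm fall in the same year. The protocol foresees that residents may know their future status when surveyed, and says this could influence some secondary outcomes. Its own sequence, survey first and second-wave package afterwards, makes that part of the bias avoidable.

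Size: not estimable from the document, in amount or direction. It is confined to self-reported secondary outcomes, with conscious knowledge the best-supported example. The effect on HIV prevalence should be close to nil, and neither the sample size nor the primary analysis changes.

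The conclusion rests on two assumptions: that year 5 means the same period for unmasking and survey, as the reference to the baseline study suggests, and that no unstated operational reason requires control residents or leaders to be told earlier. If the full protocol already places disclosure after fieldwork, only the wording of the article needs attention.

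**What to change.** Amend Allocation as follows:

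1. Define commencement of a wave as the start of its intervention, after the impact survey has been completed.
2. Before then, release the second-wave allocation only to those who must know it to organise the survey. Give field teams the list of ten districts without their wave.
3. Inform control-district leadership, residents and interviewers of second-wave status only after impact-survey fieldwork has closed in all ten districts.
4. Describe the survey in the same terms in all ten districts, in wording that still meets the Informed consent commitment to explain its nature and purpose.
5. Keep the existing acknowledgement that first-wave residents will be aware, so that the remaining asymmetry is visible to readers of the secondary results.

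Cost: a few sentences, with no change to sample, data or primary analysis. Approaches to second-wave leaders about the intervention must wait until fieldwork ends, so preparation for that wave may start somewhat later. The intervention itself is already scheduled after the survey.
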